**Methods:**

A cluster randomized controlled trial will be conducted with 176 first-year students enrolled in compulsory tennis physical education courses at The Chinese University of Hong Kong. Eight entire classes (four male and four female) will be randomly assigned to either an intervention or control group. The intervention group will play a tennis SVG, *TopSpin 2K25,* twice weekly for six weeks alongside regular PE lessons. Assessments at baseline, post-intervention, and three-week follow-up will include self-reported gaming behavior, physical activity level, PL domains, and objective tests of reaction time, eye-hand coordination, and tennis knowledge.

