## Materials and methods

### Study design

A cluster randomized controlled trial will be conducted to examine the effectiveness of participation in the tennis SVG ‘*TopSpin 2K25’* on PL among university students at the Chinese University of Hong Kong (CUHK), beyond their regular tennis PE lessons. In this context, the PE courses refer specifically to the public PE practice courses that are compulsory for non-sports majors, guided by PE teachers, which are credit-bearing. Our study employs cluster randomization at the class level, rather than individual randomization, which is commonly used in educational setting. This approach allows entire classes to be randomly assigned to either the intervention or control group, maintaining the integrity of existing class structures and minimizing disruption to timetables and teaching logistics.

A total of 176 first-year university students enrolled in tennis PE courses will be recruited. These students will be drawn from eight entire classes – four male and four female, with each class comprising 22 students. Although students self-select their PE classes during course registration, random assignment will be conducted at the class level after enrollment is finalized. The classes will be randomly assigned to either the intervention group (two male and two female classes; 88 students) or the control group (two male and two female classes; 88 students).

The intervention group will engage in two 20-min sports video gaming sessions weekly in addition to their regular PE lessons. The intervention will last for six weeks, followed by a three-week follow-up period. Data will be collected at three time points: baseline, post-intervention, and follow-up. The intervention duration of two 20-minute sessions per week was selected based on feasibility within the university schedule and supported by prior research. Röglin et al. [19] conducted a randomized controlled trial in which 15–20-minute exergaming sessions, delivered twice weekly over three months, significantly improved students’ physical self-concept, including strength, coordination, and speed. These findings suggest that even short-duration, structured gaming interventions can elicit measurable changes in physical competence and support physical literacy development.

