### Participants

#### Sample size calculation.

Given that the hypotheses in this study involve both between-subjects comparisons (intervention vs. control groups) and within-subjects measurements across three time points, the sample size was calculated using the *“ANOVA: Repeated measures, within-between interaction”* option in G*Power 3.1 software. Based on an expected medium effect size (f = 0.25), an alpha level of 0.05, and a desired statistical power of 0.80, the required sample size was determined to be 28 participants per group. The choice of f = 0.25 was informed by Cohen’s conventional benchmarks and supported by findings from related educational and exergaming interventions. For instance, Zhao et al. [21] conducted a meta-analysis of 16 randomized controlled trials involving 2,962 students and found that exergames significantly improved PE learning outcomes, with a standardized mean difference (SMD) of 0.45, which corresponds to a medium effect size. Given the educational nature of our intervention and the exploratory context, this estimate was considered both conservative and realistic. To account for an anticipated dropout rate of 20%, the target sample size was increased to 35 participants per group, resulting in a minimum total of 70 participants. To ensure sufficient power and account for unforeseen attrition, more participants than the minimum required will be recruited.

Since this study employs a cluster randomized controlled trial design, it is essential to account for the intra-cluster correlation (ICC) to avoid underestimating the required sample size. Participants within the same class may exhibit correlated outcomes due to shared learning environments and peer interactions. To adjust for clustering, we applied the design effect formula:

Design Effect=1+(m−1)×ICC

Where:

*m* = average cluster size (22 students per class)*ICC* = assumed intra-cluster correlation (conservatively estimated at **0.02** based on similar educational interventions)

Thus:

Design Effect=1+(22−1)×0.02=1+21×0.02=1.42

The adjusted sample size becomes:

70×1.42≈100 participants

To ensure adequate power and account for potential attrition and clustering effects, we plan to recruit 176 participants across 8 classes, which exceeds the adjusted minimum requirement.

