### Data analysis

Descriptive statistics, including means and standard deviations, will be calculated for university students’ video gaming time, gaming frequency, physical activity levels, physical literacy, reaction time, and eye-hand coordination across all relevant subscales and instruments. To examine baseline differences between groups in the cross-sectional study, one-way analyses of variance (ANOVAs) will be conducted.

To evaluate intervention effects, mixed-effects models will be employed instead of simple repeated-measures ANOVAs to account for the hierarchical structure of the data and potential intra-cluster correlation among participants within the same class group. This approach addresses the reality that, although courses follow standardized content, variability in teaching style, instructor enthusiasm, and informal reinforcement of the intervention is inevitable in real-world PE settings. Mixed-effects models will include fixed effects for time (baseline, post-intervention, follow-up) and group (intervention vs. control), as well as random effects for class clusters to capture variability across different teaching contexts. These models will assess both main effects and interaction effects, providing more accurate standard error estimation and valid statistical inference.

For secondary outcomes (motivation, cognitive knowledge, social engagement, and physical activity), similar mixed-effects or generalized estimating equation models will be applied, depending on distributional assumptions. Multiple linear regression analyses will explore predictive relationships between PL and physical activity levels, with SVG gaming included as a potential mediator or moderator. Covariates such as baseline physical activity, prior SVG experience, and demographic characteristics (age, gender) will be adjusted for in all models. Interaction effects between the intervention and participant characteristics (e.g., gender, gaming experience) will also be examined to identify subgroup differences.

To enhance the interpretability and transparency of our findings, partial eta-squared will be reported for all primary outcomes to indicate the magnitude of observed effects. Additionally, 95% confidence intervals will be provided to reflect the precision of the estimates and the range within which the true effect is likely to fall. These metrics will support a more nuanced understanding of the intervention’s impact and facilitate comparison with other studies.

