To ensure the integrity of the analysis, the following procedures will be used to address missing data. Participants with more than 20% missing responses on key outcome measures (e.g., physical literacy or physical activity questionnaires) may be excluded from specific analyses. All decisions regarding missing data handling will be documented in the final report, including the rationale for exclusion or imputation. All statistical analyses will be performed using SPSS Version 30 for Windows, with the significance level set at *p* < 0.05.

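### GEE is allowed for the four secondary outcomes on distributional grounds alone, although only eight classes are randomised

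*Protocol article*

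**What the plan says.** The design is a cluster trial with few clusters. The abstract states: "Eight entire classes (four male and four female) will be randomly assigned to either an intervention or control group". Study design adds: "These students will be drawn from eight entire classes – four male and four female, with each class comprising 22 students", and divides them into "the intervention group (two male and two female classes; 88 students) or the control group (two male and two female classes; 88 students"). That is four classes against four.

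The Data analysis section first describes mixed-effects models with fixed effects for time and group, their interaction, and random effects for class. It then turns to a named set of outcomes: "For secondary outcomes (motivation, cognitive knowledge, social engagement, and physical activity"). For these, "similar mixed-effects or generalized estimating equation models will be applied, depending on distributional assumptions". Age and gender, among other covariates, are to be adjusted for in all models. The section closes with: "All statistical analyses will be performed using SPSS Version 30 for Windows, with the significance level set at" p < 0.05.

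For the GEE branch the article states neither the clustering unit (class or student), nor the variance estimator, nor the reference distribution. The sample size section does allow for class correlation, with "average cluster size (22 students per class") and an ICC "conservatively estimated at 0.02 based on similar educational interventions".

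**The concern.** The rule for moving to GEE looks at the wrong feature of the data. A skewed or bounded outcome may be a reason to leave a normal-theory model. Whether the usual GEE test keeps its error rate depends on how many independent clusters there are. With eight, the plain sandwich variance is too small on average, and the normal or chi-square reference takes no account of how imprecisely that variance is estimated.

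The GEE branch is a live option. Weekly MET-minutes and a ten-item quiz score can both plausibly fail a normality check. The four outcomes carry four of the five hypotheses in the Introduction. If the default form of GEE were used, an outcome could be declared improved by a test with a real error rate about three to five times the stated 0.05, and its confidence intervals would be too short. The two permitted model families would also differ in real error rate.

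**Working it through.** **Inputs from the article.** Eight classes, k = 4 per arm; 22 students per class; three time points and two groups, so the group-by-time test has 2 df and a single change contrast 1 df; ICC 0.02; alpha 0.05 (taken as two-sided, which the article does not state).

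**The plan's own figure.** The article gives no error rate for GEE beyond the nominal 0.05. Its clustering adjustment reproduces: 1 + 21 × 0.02 = 1.42, and 70 × 1.42 = 99.4, about 100.

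**A. GEE clustered on class, uncorrected sandwich, z or chi-square reference.** With equal class sizes the contrast is a comparison of four class means with four. The uncorrected sandwich variance is (k − 1)/k = 3/4 of the unbiased one, which has 6 df.
- 1 df: P(|t6| > 1.96 × √0.75) = P(|t6| > 1.697) = **14.1%**.
- 2 df: the Wald statistic is 8/6 times Hotelling's T² on 6 df, so the rate is P(F(2,5) > 5.991 × 0.75 × 5/12) = P(F(2,5) > 1.872) = **24.7%**.
- Interval width, 1 df: 1.697/2.447 = 0.69 of the correct width.
- Group main effect adjusted for gender, which is constant within a class: P(|t5| > 1.96 × √(5/8)) = P(|t5| > 1.550) = 18.2%.

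The 1-df and 2-df results do not depend on the ICC. Simulation with an independence working correlation (4,000 runs per setting; ICC 0, 0.02 and 0.10; with and without covariates) gave 13.6–14.8% and 24.7–25.6%. A skewed outcome gave 13.8–14.8% and 25.0%. Exchangeable GEE fits (600 runs) gave 14.3% and 22.7%.

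**B. Partial corrections, still clustered on class.**

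| Variance | Reference | 1 df | 2 df |
|---|---|---|---|
| uncorrected | z / chi-square | 14.1% | 24.7% |
| uncorrected | t6 | 7.8% | – |
| × k/(k − 1) | z / chi-square | 9.8% | 17.7% |
| × k/(k − 1) | t6 | 5.0% | – |

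For the 2-df test with corrected variance, the exact reference is Hotelling's: W × 5/12 against F(2,5). Taking W/2 against F(2,6), critical value 5.143, still gives P(F(2,5) > 5.143 × 2 × 5/12) = 8.2%.

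**C. GEE clustered on the student, class ignored.**
- Comparison at one time point, ICC 0.02: 2Φ(−1.96/√1.42) = **10.0%**.
- Change contrast, class effects constant over time: they cancel, and simulation gives 5–6%.
- Change contrast, class effects varying over time (variance **assumed**, total variance 1, within-person correlation 0.5 assumed): a student's change has variance about 1. A class-by-time variance of 1% adds 0.02 to the between-class variance of change, so the inflation is 1 + 21 × 0.02 = 1.42 and the rates are 10.0% (1 df) and exp(−5.991/2.84) = 12.1% (2 df). At 2% the inflation is 1 + 21 × 0.04 = 1.84, giving 14.8% and exp(−5.991/3.68) = 19.6%. Simulations gave 11–14% and 16–22% across the two tests.

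**D. Would any mixed model do?** No. One with only class and person intercepts has the same gap as case C. Simulation (10,000 runs) gave 4.8% / 5.4% (1 df / 2 df) with no class-by-time variance, 9.4% / 11.9% at 1% and 15.0% / 19.7% at 2%. A t-test on class-mean change with 6 df held 4.7–5.2% throughout.

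**The case against.** The strongest reply is that the article does not commit to the settings that produce 14–25%. GEE must be chosen, clustered on class, with an uncorrected sandwich and a large-sample reference. A condensed article commonly leaves the variance estimator and denominator df to a full protocol or SAP, which is not shown. GEE with suitable corrections is defensible even here. All of this stands, so the absence of a named correction is not the point. What the article does state is the selection criterion, and that criterion ignores the number of clusters.

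A reader might go further in four ways that the text does not support.
- That the plan promises valid inference from GEE: that assurance closes the paragraph on mixed models, and GEE appears only in the next one.
- That the model will be picked after looking at the data: the wording can equally mean a choice by outcome type, fixed in advance.
- That clustering on the student is bound to inflate error for change contrasts: this needs class effects that vary over time. The article gives no such variance. Its 0.02 is an ordinary ICC and cannot be borrowed for this, although its remarks on varying teaching style and enthusiasm make some variation plausible.
- That GEE is unsafe and mixed models are safe: part D shows that the random-effects structure matters as much as the model family.

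The article also calls its cognitive and social engagement measures exploratory, which lowers the stakes for two of the four outcomes.

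**Conclusion.** The point holds in conditional form. The plan opens a GEE route for four secondary outcomes on distributional grounds, with four classes per arm. In its uncorrected class-clustered form that route has a true error rate of about 14% (1 df) or 25% (2 df), whatever the ICC. Clustered on the student, it drops the class correlation that the sample size section treats as essential: about 10% for a single-time comparison at ICC 0.02, about 5% for change if class effects are stable, and more if they are not, by an amount that rests on assumed values. The closed forms assume equal class sizes and a two-sided 5% test. It does not follow that four of five hypotheses will be tested at the wrong level, since that would require the worst form of GEE for every outcome. Because this is an optional model for secondary outcomes, it is something that should be fixed, not a fatal flaw.

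**What to change.** Replace the GEE option with an analysis that is valid for eight clusters, named in advance for each outcome:

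1. A t-test or regression on class-mean change scores, four classes against four, with about 6 df (5 if gender is included); or
2. A linear or generalised linear mixed model with random effects for class, class-by-time and person, and small-sample denominator df (Satterthwaite or Kenward–Roger where available). A log scale can be considered for skewed MET-minutes.

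If GEE is kept, cluster on class, name the bias-corrected sandwich variance, and refer to t or F with about 6 df (5 with gender). For the 2-df interaction, use the Hotelling form in part B. Both the variance correction and the reference distribution are needed. Confirm that the planned software supplies them; option 1 needs nothing special.

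The change is a few sentences of analysis text, with no effect on recruitment, data collection or conduct. The cost is wider confidence intervals and less apparent power on the secondary outcomes. A class-by-time component may also be poorly estimated from eight classes, which favours option 1 as the fallback.

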While existing research has largely focused on the affective and cognitive benefits of SVGs, there remains a notable gap in studies exploring their influence on physical competence and the social domains of PL [17]. Crucially, the PL construct consists of four interrelated elements (motivation/confidence, physical competence, knowledge/understanding, engagement in physical activities for life) and respective domains (affective, physical, cognitive, behavioral) [18]. Improvements in one domain can positively influence others; for example, greater motivation may increase activity participation, enhancing physical competence and confidence, while deeper sport-specific knowledge can foster meaningful social interactions. SVGs, by stimulating motivation and cognitive engagement, may serve as a catalyst for holistic PL development. Moreover, gameplay often involves perceptual-motor demands such as reflexes and coordination and incorporates cooperative or competitive social interactions. These considerations underscore the need for interventions addressing all PL domains rather than focusing narrowly on motivation or knowledge.

In this study, simple reaction time and eye–hand coordination were selected as outcome measures because they represent targeted components within the physical domain of PL and align with the perceptual–motor demands of both video gaming and real-life tennis. While these measures do not capture comprehensive motor competence, they provide insight into specific physical attributes that may be influenced by the intervention.

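### If SVG gaming means the allocated intervention, the mediator option in the exploratory regression reverses the trial's own chain, and the single-level method named understates the error of a class-assigned SVG term

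*Protocol article*

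**What the plan says.** The protocol article's Data analysis section evaluates the intervention with mixed-effects models, chosen to "account for the hierarchical structure of the data and potential intra-cluster correlation among participants within the same class group". They carry fixed effects for time and group "as well as random effects for class clusters to capture variability across different teaching contexts". Secondary outcomes get similar mixed or GEE models.

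A separate sentence then describes another analysis: "Multiple linear regression analyses will explore predictive relationships between PL and physical activity levels, with SVG gaming included as a potential mediator or moderator". It names no class term. The next sentence reads: "Covariates such as baseline physical activity, prior SVG experience, and demographic characteristics (age, gender) will be adjusted for in all models". Class is not in that list, although the list is open-ended.

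The Introduction gives the theory in the other direction. On the first link: "SVGs, by stimulating motivation and cognitive engagement, may serve as a catalyst for holistic PL development". On the second: "greater motivation may increase activity participation, enhancing physical competence and confidence". Exposure to SVG sessions is set by design. Under Study design: "The classes will be randomly assigned to either the intervention group" or to control. The Intervention section gives controls no sessions and advises them against playing tennis video games.

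SVG gaming is not defined in the regression sentence. The Data collection section also collects self-reported weekly time and days of SVG play, put only to participants who report regular gaming.

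**The concern.** A mediator of the relation between PL and activity has to be something that PL brings about. In this trial, access to SVG sessions is brought about by drawing lots among classes. If SVG gaming means that allocation, the mediator option gives the randomised exposure the role that the trial's theory gives to PL. The resulting indirect effect would not show whether gains in PL account for a change in activity, and could be published as if it did.

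The second part is the method. Multiple linear regression treats the 176 students as independent, while the same section argues that students in one class are correlated. A term that is constant within class is where ignoring class does most harm to a standard error.

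**Working it through.** **Inputs.** From the sample size calculation: m = 22 per class, 8 classes, 176 students, ICC = 0.02, two-sided alpha 0.05. Assumed here: ICCs of 0.05 and 0.10 as a range, and illustrative path sizes for step 2.

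**1. The plan's own figure.** Design effect = 1 + (m − 1) × ICC = 1 + 21 × 0.02 = 1.42, and 70 × 1.42 = 99.4, rounded up to 100. Both agree with the protocol.

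**2. Order of the mediation, with SVG gaming read as allocation.** Assume the Introduction's chain is true, with allocation to PL = 0.45, PL to activity = 0.30, no direct effect of allocation on activity, and residual variances of 1.

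- Chain order (group, PL, activity): indirect effect = 0.45 × 0.30 = 0.135. A large simulated sample gives 0.135.
- Regression order (PL, SVG, activity), PL measured after the intervention: the first path is cov/var = (0.45 × 0.25)/(1 + 0.45² × 0.25) = 0.1125/1.0506 = 0.107. The second path, SVG to activity given PL, is zero because all of the effect passes through PL. The product is about 0.000 (simulated 0.0004), although the mechanism is fully present.
- If allocation also had a direct effect c on activity, the same product would be 0.107 × c. An effect of the games that bypasses PL would then appear as PL acting through the games.
- Regression order with baseline PL: randomisation makes the first path zero in expectation (simulated slope 0.000), so the indirect effect is zero whatever the truth.

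**3. Class left out of the regression.** For a term constant within class, the true standard error is √DE times the naive one, and the actual error rate of a nominal 5% test is 2 × (1 − Φ(1.96/√DE)).

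| ICC | DE | √DE | Naive SE too small by | Actual error rate |
|---|---|---|---|---|
| 0.02 (protocol) | 1.42 | 1.19 | 16% | 10.0% |
| 0.05 (assumed) | 2.05 | 1.43 | 30% | 17.1% |
| 0.10 (assumed) | 3.10 | 1.76 | 43% | 26.6% |

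For a variable that differs between students, such as PL, the design effect is 1 + (m − 1) × ICC(PL) × ICC(activity). With 0.02 for both this is 1 + 21 × 0.0004 = 1.0084, an SE ratio of 1.004.

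Simulated ordinary regression, 8 classes of 22, 10,000 runs, all effects null, equal ICC for PL and activity:

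| ICC | Group main effect | PL slope | PL-by-group interaction | Both mediation paths significant |
|---|---|---|---|---|
| 0.02 | 9.9% | 5.0% | 5.3% | 1.0% |
| 0.05 | 16.6% | 4.9% | 5.2% | 2.8% |
| 0.10 | 27.0% | 7.1% | 6.5% | 7.2% |

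A separate simulation of the first two test columns agreed within 0.3 percentage points. The last column is consistent with two class-assigned tests multiplied together: at ICC 0.02, 0.10 × 0.10 = 0.010, where correctly sized tests would give 0.05 × 0.05 = 0.0025. It is low because both paths are null. If one path were real and well powered, the rate would approach that of the other path, about 10% when that path is the class-assigned one.

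**The case against.** Several points on the other side stand.

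- The sentence offers mediator or moderator. Asking whether the association of PL with activity differs by SVG gaming is coherent under any meaning of the term.
- The regressions are offered as exploratory and predictive. All five hypotheses in the Introduction compare change between groups, and none concerns mediation. A reader might infer that this regression is how the trial means to test its mechanism; the document does not say so, and the Introduction's chain is hedged rationale.
- SVG gaming may mean self-reported play. A reader might infer that exposure and mediator are swapped under that reading too. This does not follow for the baseline measure, which is taken in the recruitment lesson, whereas assignment comes after enrolment is final. Play reported after baseline is post-randomisation, but nothing in the document shows how far arm determines it.
- Omission of class is inferred from the method's name and from silence. The covariate list is open, and a journal article may leave such detail to a fuller plan.
- The 10% applies to one kind of term. A reader might infer that every standard error in the regression is wrong. At ICC 0.02 the PL slope, which is the relation the sentence is about, and the interaction are close to nominal.

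What does not answer the point: the mediator option is expressly kept, and with SVG gaming as allocation it cannot be interpreted with either baseline or post-intervention PL. The method is also positively named as a single-level one, directly after clustering has been given as the reason for mixed models.

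**Conclusion.** The point holds in a limited form. If SVG gaming means the allocated intervention, the mediator option reverses the order of the Introduction's chain, and its indirect effect is either zero by randomisation or without causal meaning. This rests on the design alone; the contrast of 0.000 with 0.135 only illustrates it under assumed paths. If the regression is run without class, a test of a class-assigned SVG main effect runs at about 10% at the protocol's ICC, and at about 17% and 27% at assumed ICCs of 0.05 and 0.10. The PL slope and the PL-by-group interaction are nearly unaffected at 0.02.

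The models for intervention effects, with their class random effects, are not touched, so this is no ground to doubt the main results. It should be corrected because it decides what the exploratory analysis can conclude.

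**What to change.** Revise the regression sentence in Data analysis as follows.

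1. State whether SVG gaming means allocated group or self-reported play and, if the latter, at which time point.
2. Drop SVG gaming as mediator of the relation between PL and activity. If mediation is of interest, take allocated group as exposure, PL at Week 8 on one named instrument (for example the PPLI) adjusted for its baseline as mediator, and physical activity at Week 11 adjusted for its baseline as outcome. Label it exploratory.
3. Keep SVG gaming as moderator only if that is a question the trial wants to ask.
4. Include the class random effect in these models, as in the intervention-effect models, with small-sample degrees of freedom. Eight classes in two arms leave at most 8 − 2 = 6 for a class-assigned term.

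The cost is wording and slightly more analysis work. PL and activity are already scheduled at all three time points, so no new data are needed. Intervals for the SVG term will be wider: the standard error alone rises by a factor of about 1.19 at ICC 0.02.

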*Physical Competence***:** Participants in the intervention group will demonstrate greater improvement in perceptual-motor skills, specifically simple reaction time and eye-hand coordination, compared to those in the control group. These measures represent targeted components within the physical domain of PL and align with the perceptual-motor demands of both sports video gameplay and real-life tennis, rather than comprehensive motor competence.*Motivation for real-life sports***:** Participants in the intervention group will report a greater increase in motivation to engage in real-life sports compared to those in the control group.*Cognitive knowledge of tennis:* Participants in the intervention group will achieve a greater improvement in cognitive knowledge related to tennis than participants in the control group.*Social engagement in physical activities*: Participants in the intervention group will exhibit greater enhancement in in-person social interaction relative to the control group.*Physical activity engagement:* Participants in the intervention group will show a higher increase in physical activity engagement levels than their counterparts in the control group.

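### Baseline is a response time and baseline physical activity is also a covariate in all models: the adjustment leaves the group-by-time estimate unchanged, and the precision available from each outcome's own baseline is forgone

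*Protocol article*

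**What the plan says.** All of the model wording is in the Data analysis section of the protocol article.

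- Model: "Mixed-effects models will include fixed effects for time (baseline, post-intervention, follow-up) and group (intervention vs. control), as well as random effects for class clusters". Baseline is thus a level of the response. Class is the only random effect named.
- Effects assessed: "These models will assess both main effects and interaction effects".
- Adjustment: "Covariates such as baseline physical activity, prior SVG experience, and demographic characteristics (age, gender) will be adjusted for in all models".
- Physical activity is itself an outcome. The list of secondary outcomes begins "For secondary outcomes (motivation, cognitive knowledge, social engagement, and physical activity", and for these "similar mixed-effects or generalized estimating equation models will be applied, depending on distributional assumptions".

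The hypotheses at the end of the Introduction are about change. For physical competence, the intervention group "will demonstrate greater improvement in perceptual-motor skills, specifically simple reaction time and eye-hand coordination, compared to those in the control group". The other four have the same form, so the matching test is group by time.

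**The concern.** Baseline adjustment in a randomised trial is meant to remove outcome variation that was already present before treatment. Here the named baseline covariate sits beside a response vector that includes baseline. It acts equally on all three times, so it cannot sharpen a contrast between times. The variable that would sharpen it is the outcome's own baseline value, used as a covariate or through a common baseline mean. The article names neither use.

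The wording also covers the physical activity model, where baseline IPAQ would stand on both sides of the equation.

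At stake is efficiency. With four classes per arm, chance baseline differences between arms are plausible. A difference in change subtracts such a difference in full, whereas own-baseline adjustment subtracts only the fraction r of it.

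**Working it through.** The plan states no figure on this point, so there is none to reproduce. The within-person correlation r is needed and is not given. The sample size section lists its inputs as "Based on an expected medium effect size (f = 0.25), an alpha level of 0.05, and a desired statistical power of 0.80", with no correlation. r is therefore assumed at 0.3, 0.5 and 0.7. Variances are in units of the outcome variance, taken as equal at all times.

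**1. Effect of a time-constant covariate on the tested contrast.** Let the mean for participant i at time t be a + b·group + c(t) + d(t)·group + g·x(i), where x is baseline physical activity. The change from baseline to t contains g·x(i) - g·x(i) = 0. With complete data, the estimate of d(t) is the difference between arms in mean change, whatever x is.

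A simulated data set with the trial's layout (8 classes of 22, three times, r = 0.5, small class effect, all parameter values assumed) gave these results for the group-by-time term at the post-intervention time:

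| Random effects | Covariate | Estimate | SE |
|---|---|---|---|
| class and participant | none | 0.28125 | 0.1486 |
| class and participant | baseline physical activity | 0.28125 | 0.1486 |
| class and participant | own baseline | 0.28125 | 0.1486 |
| class only, as written | none | 0.28125 | 0.2029 |
| class only, as written | baseline physical activity | 0.28125 | 0.1908 |
| class only, as written | own baseline | 0.28125 | 0.1612 |

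The estimate is the same in every row. Under the class-only model the printed SE falls because the covariate absorbs participant variation that this model leaves in the residual. Since the estimator has not changed, neither has its true sampling variance.

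**2. Limits of that result.** In the same simulation:
- The group main-effect coefficient moved from 0.199 to 0.105 under the class-only model when baseline physical activity was added.
- With about 19% of post-baseline visits missing, the interaction moved from 0.410 to 0.419 with class and participant intercepts, and from 0.433 to 0.441 with class only.
- The algebra in step 1 does not carry over to GEE with a non-linear link.

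**3. Precision forgone.** For one post-baseline time, within class:
- Change from baseline: 2(1 - r).
- Own baseline as covariate: 1 - r².
- Ratio: (1 - r²) / [2(1 - r)] = (1 + r)/2, a reduction of (1 - r)/2.

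| r (assumed) | Change | Own-baseline adjusted | Reduction |
|---|---|---|---|
| 0.3 | 1.40 | 0.91 | 35% |
| 0.5 | 1.00 | 0.75 | 25% |
| 0.7 | 0.60 | 0.51 | 15% |

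**4. The physical activity model.** Regress the three IPAQ responses on baseline IPAQ with one common slope, at r = 0.5. The slope that applies at baseline is 1, and at each later time it is 0.5.
- Pooled slope: (1 + 0.5 + 0.5)/3 = 0.67, against 0.5 at Weeks 8 and 11.
- Residual variance at baseline: (1 - 2/3)² = 0.11.
- Residual variance at each later time: 1 + (2/3)² - 2 × (2/3) × 0.5 = 0.78.

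The residual variance is thus seven times larger after baseline than at it. By step 1, the distorted slope still cancels from the group-by-time estimate.

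**The case against.** The strongest reply is that a group-by-time model with baseline as a response is an accepted analysis. It matches hypotheses worded as improvement, it matches the interaction on which the sample size was based, and it is unbiased under randomisation. That stands: the choice is less efficient, not invalid.

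Other parts of the reply also stand:
- A reader might infer that the trial ignores each outcome's own baseline. It does not. That baseline is the first response, and the interaction measures change from it. The covariate list is also open-ended.
- A reader might infer that using baseline IPAQ twice biases the physical activity result, or that the baseline row is fitted perfectly. Neither follows. The distorted slope is a nuisance coefficient, and a common slope of 0.67 leaves a residual variance of 0.11 at baseline.
- A reader might infer that the covariates are useless everywhere. The cancellation is limited as step 2 of the working shows, and in the planned regression and subgroup analyses the covariates can do ordinary work.
- The size rests on an assumed r and leaves out between-class variance. No loss of power has been shown, and the planned 176 participants exceed the article's own minimum of about 100.

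The open-ended list does not remove the overlap in the physical activity model, because baseline physical activity is named and is to go into every model.

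**Conclusion.** The point holds as one of efficiency and clear specification. For a linear model with complete data, adjusting for baseline physical activity does nothing to the estimate that the hypotheses concern, which stays an unadjusted difference in change. Using the outcome's own baseline would lower within-class variance at one post-baseline time by 15% to 35% for r between 0.7 and 0.3. That range assumes equal variances over time and a modelled within-person correlation, and between-class variance would dilute it.

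In the physical activity model, baseline IPAQ has two incompatible roles. The result is a distorted common slope and unequal residual variances. The documents do not support a claim of bias in the interaction, for this or any other outcome.

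**What to change.** Give baseline one role and state it in the Data analysis section.

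- Option A: model Weeks 8 and 11 as the responses, with that outcome's own baseline (slope allowed to differ by time), gender, age and prior SVG experience as covariates.
- Option B: keep baseline as a response and constrain the two arms to a common baseline mean.

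Under either option, do not enter baseline physical activity as a covariate in any model that has baseline IPAQ among its responses. Both options need the correlation between a participant's repeated measurements to be modelled as well as the class effect; in Option B the gain depends on it.

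The cost is a change of wording. Every value needed is already to be collected, and no visit, measurement or participant is added.
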